### **5.5.3 Randomisation: blinded treatment. Group allocation**

Following enrolment, participants will be randomised to either the intervention or placebo group. Random assignment will be performed by [name]. To ensure balanced groups for interim safety analysis, we will utilise a block randomisation technique, with permuted blocks of 30 for each study centre and for previous antibiotic use (15 to group 1 and 15 to group 2 per block), until sample size criteria are met.

Participants, medical and nursing staff, and investigators (study field staff) will also be blinded to allocation for the probiotic or placebo. The study code will be kept by the study statistician who will have no clinical role and no contact with patients.

After the study's opening assessment is completed (section 5.5.2), the randomisation list will be forwarded to the product distributor (Yakult Europe BV) by the Trial Statistician. Yakult Europe B.V. will arrange for product packs to be delivered, each with a sticker / code specific for each participant. This will ensure the hospital researchers are blinded to verum or placebo.

The placebo will be in identical packaging and of similar appearance and taste. The placebo has been used in several European studies and proven to be effective for blinding purposes.

Study field staff will be unaware to which group the subjects are assigned. See Appendix 5 for the decision tree outlining recruitment and randomisation of subjects. The study code will be kept by the study statistician who will have no clinical role and no contact with patients. Communications via electronic means will be encrypted (AES256), as per Instauration's Standard Operating Procedure.

### **5.5.4 Product Delivery**

Intervention samples will be sent in 15-bottle packs, with a sticker on the front with:

- the name of the PI
- 'Yakult/placebo'
- Patient code
- Best before date

A full set of instructions and dates will be sent. Deliveries (sufficient for two weeks supply per patient) will be every other week on a Tuesday. Orders should be made to [name] ([[contact]](mailto:[contact])), copying [name] ([[contact]](mailto:[contact])), and [name] ([[contact]](mailto:[contact])). The deadline for ordering is the Wednesday of the week before, six days before the delivery date.

The deliveries will always include a few spare bottles for checking the temperature on receipt. If the temperature is above 7°C, further bottles should be checked. If the whole consignment is at too high a temperature, do not give them to the subjects but inform the above people immediately. They will arrange a second delivery (arriving Wednesday, the next day). This ensures the supply to the patient should not be interrupted. Each site will ensure the fridge is locked and accessed only by study personnel.

### **5.5.5 Administration of intervention**

Participants will receive the study drink within 48 hours of their first dose of antibiotics therapy. After that, participants will receive the verum (probiotic LcS) or placebo drink (65 ml bottle) once a day, according to the randomisation schedule. The study drink will be given by a nurse at drug round.

A schematic representation of the study phases & timeline is presented in *Study flow chart* (Appendix 1 and 2)

Compliance will be monitored throughout the study. As this trial involves inpatients who have proved very compliant in the previous study (Wong *et al* 2014), compliance is defined as follows:

**Minor non-compliance:** 2 consecutive days not drinking the study intervention;

**Major non-compliance:** 3 consecutive days not drinking

**If a patient misses intervention for more than 3 days, they will be withdrawn from the study.**

We will analyse the data using intention-to-treat principle.

An episode of diarrhoea is defined as two or more liquid stools (Bristol Stool Scale types 5, 6 and 7) that is greater than normal for the inpatient over a 24 hour period.

The frequency and duration of diarrhoea / constipation will be monitored.

Patients' quality of life will be assessed by WHO-QoL BREF questionnaire. Furthermore, medication charts (especially antibiotics, laxatives, anti-diarrhoeal agents, proton pump inhibitors and H2 blocker) and nutrition risk scores (Wong *et al.* 2010, 2012) will be assessed at baseline, 7 days after finishing course of antibiotics and 30 days after finishing course of antibiotics (follow up).

Duration of hospital stay will be recorded on the patients' hospital record.

Bowel function will also be monitored throughout (i.e. stool type; duration of diarrhoea / constipation relapse) by health care staff.

In addition, faecal samples will be routinely acquired at **baseline (within 24 hours of starting intervention, Yakult/placebo), 7 +/- 3 days after finishing course of antibiotics, at follow up (30 +/- 3 days after finishing course of antibiotics), and in the event of diarrhoea.** Study samples will only be collected and processed Mon-Fri, therefore a window period of +/- 3 days for the day 7 and day 30 post-antibiotics course. These samples will be frozen and stored, before sending to YHER for microbiological analysis, including TaqMan PCR analysis of toxigenic *C. difficile*. Technique will be based on the paper by Kubota *et al.* (2014).

Faecal samples from any patient developing diarrhoea will be tested by the hospital according to normal practice and a further sample stored for further analysis by the external laboratory (YHER).

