## **7.2 Sample size considerations**

Based on pilot data, this study aimed to find a difference of 17.9% in the proportion of patients with diarrhoea in two groups, (i) those on proton pump inhibitors – 56.3% and (ii) those on LcS – 38.4%. With  $\alpha=0.05$  and power of 90%, we estimate a sample size of 162 per group. After accounting for dropouts at 10% (across the length of the trial) this will require 180 per arm (total  $n=360$ ).

This sample size calculation is based on data from a single study site, but it seems reasonable to extrapolate the findings to other UK SCI centres. Therefore we aim to recruit 360 (180 per arm) in the proposed trial.

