## **7.4 Statistical analysis**

We will analyse the data using intention-to-treat principle. Fisher's exact test and  $\chi^2$  test will be used to compare rates of diarrhoea, as well as rates of AAD and CDAD. Relative risk and the number needed to treat, both with 95% confidence intervals, will be used to describe the treatment effect of probiotic. Logistic regression will be used to establish which factors influence the occurrence of diarrhoea. Continuous outcome measures will be analysed utilising ANCOVA (controlling for baseline scores and existing group differences) and multiple regression analyses ( $p<0.05$  critical value; sample size covers this analysis to a sufficient power level).

To reduce the bias implicit in utilising only complete cases, multiple imputation procedures for the laboratory data will be used using the SPSS (SPSS version 15, Inc, Chicago, IL) Markov Chain Monte Carlo multiple imputation function to produce 10 imputed datasets. These will then be analysed as normal; thereafter standard multiple

imputation procedures were used to combine the multiple scalar and multivariate estimates quantities.

To minimise confounding factors with respect to incidence of AAD and CDAD, stratification will be performed at the time of recruitment according to the antibiotic background (i) patients who have not previously received antibiotics in the 30 days prior to administration of intervention ('antibiotic-naïve') and (ii) patients who had been given a single antibiotic treatment for prophylactic purpose >14 days before first administration of intervention ('prophylactic-antibiotic').

In addition, a sub-group analysis will be performed on both treatment arms to analyse the following for association with AAD/CDAD occurrence: (i) risk of undernutrition, (ii) use of proton pump inhibitor, (iii) age  $\geq 65$  years and (iv) those receiving study drink within 24 hrs vs 48 hrs of first dose of antibiotics.

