### **14.2 Removal of Patients from the study**

Patients will be removed from the study whenever it is necessary to safeguard their health and welfare. Non-compliance with the protocol or occurrence of significant adverse events may also necessitate discontinuation from the study. When a patient is permanently removed from the study, a study closing assessment should be performed if possible, and all results must be obtained. Patients removed from the study because of an adverse event will be followed-up until the adverse event has resolved.

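### Withdrawal from the study for missed drinks ends AAD follow-up with no provision to day 30, which conflicts with the stated intention-to-treat analysis

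*Protocol*

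**What the plan says.** Section 5.5.5 grades non-compliance by consecutive days without the drink: two days is minor and "3 consecutive days not drinking" is major. It then adds: "If a patient misses intervention for more than 3 days, they will be withdrawn from the study". The withdrawal is from the study, not only from the drink. The next sentence, repeated in 7.4, reads: "We will analyse the data using intention-to-treat principle".

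Section 14.2 is softer on whether a patient leaves: "Non-compliance with the protocol or occurrence of significant adverse events may also necessitate discontinuation from the study". On data at removal it says: "When a patient is permanently removed from the study, a study closing assessment should be performed if possible, and all results must be obtained". Follow-up beyond removal is stated only for patients removed because of an adverse event, and only until that event resolves.

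Section 6.1 defines the primary outcome as AAD up to 30 days after antibiotics finish. (The synopsis counts the 30 days from the end of the study drink.) The drink is scheduled to stop 7 days after antibiotics. Section 7.2 sizes the trial at 162 per group and continues: "After accounting for dropouts at 10% (across the length of the trial) this will require 180 per arm".

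**The concern.** An intention-to-treat comparison needs the primary outcome in everyone randomised, whatever their adherence. The rule in 5.5.5 ends participation because of something that happens after randomisation. Drinks can be missed because of gut symptoms, intercurrent illness or becoming nil by mouth, and each of these can be related to diarrhoea. If outcome collection ends with participation, the patients left unobserved are a selected group, and the selection can differ between arms.

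This belongs in the protocol. An analysis plan can choose how to handle missing AAD outcomes, but it cannot recover follow-up that the protocol brought to an end.

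**Working it through.** **1. Does any section restore the follow-up?**

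| Situation | Provision after removal or stop |
|---|---|
| Missed drinks (5.5.5) | Withdrawn from the study; no later follow-up stated |
| Any permanent removal (14.2) | Closing assessment if possible; all results to be obtained |
| Removal for an adverse event (14.2) | Followed until the event resolves |
| Early termination of the whole trial (14.3) | All enrolled patients followed to the last visit |

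The 14.2 wording most naturally secures what exists at removal. It does not say that AAD is followed to day 30. Section 14.3 shows that the protocol can state such a provision when it intends one.

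**2. How much of the window is unobserved?** The drink ends 7 days after antibiotics and the 6.1 window ends at day 30. A patient withdrawn while still due to take the drink, and free of AAD, loses at least 30 − 7 = 23 days. On the synopsis definition the loss is at least 30 days.

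**3. The plan's own sample size.** Inputs from 7.2: p1 = 0.563, p2 = 0.384, α = 0.05 (taken as two-sided), power 90%. With mean rate p̄ = 0.4735:

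n = [1.960·√(2p̄(1−p̄)) + 1.282·√(p1(1−p1) + p2(1−p2))]² / (p1−p2)² = 161.4, rounded up to 162.

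162 / (1 − 0.10) = 180. Both figures reproduce, so the sizing arithmetic is not at fault.

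**4. Upper illustration.** Assumption: the whole 10% dropout allowance, 18 per arm, has an unobserved outcome, and the 162 observed per arm show the planned rates.

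- Observed events: 162 × 0.563 = 91.2 on placebo and 162 × 0.384 = 62.2 on LcS.
- All lost LcS patients have AAD and no lost placebo patient does: 91.2/180 − (62.2 + 18)/180 = 6.1 points (z = 1.16, p about 0.25).
- The reverse: (91.2 + 18)/180 − 62.2/180 = 26.1 points.
- Lost patients in both arms at the 56.3% rate: LcS becomes 0.9 × 0.384 + 0.1 × 0.563 = 0.402, and the difference is 0.563 − 0.402 = 16.1 points.

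**5. Bias if only observed patients were analysed.** Assumptions: no true effect (56.3% in both arms), 10% withdrawn per arm, withdrawn placebo patients at 56.3%.

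- Withdrawn LcS patients at 80%: observed LcS rate (0.563 − 0.1 × 0.80)/0.9 = 0.537, a spurious benefit of 2.6 points.
- Withdrawn LcS patients at 100%: (0.563 − 0.1)/0.9 = 0.514, a spurious benefit of 4.9 points.
- With 5% withdrawn, the same range is 1.2 to 2.3 points.
- With the 80% risk in withdrawn placebo patients instead, the 10% case reverses to −2.6 points.

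**6. The trigger.** The compliance grades count consecutive days; the withdrawal rule does not say whether its days are consecutive. Illustration, assuming 21 drink days and independent misses at daily rate q. Four or more missed days in total has probability 1 − P(Bin(21, q) ≤ 3). A run of four has probability of about q⁴(1 + 17(1 − q)).

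| Assumed daily miss rate | 4 or more in total | 4 in a row |
|---|---|---|
| 5% | 1.9% | 0.01% |
| 10% | 15% | 0.2% |

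The two readings withdraw very different numbers of patients.

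**The case against.** Several stronger readings are tempting, and the protocol does not support them.

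- A reader might infer that withdrawn patients' AAD data are discarded, or that the primary endpoint is analysed in completers. No section says so, and 5.5.5 and 7.4 say intention to treat. AAD is a yes/no occurrence, so a patient with AAD before removal already has a known outcome. Only patients event-free at removal are unresolved. Section 14.2 also requires all results to be obtained.
- Inflating 162 to 180 is routine sizing. It does not define an analysis set.
- Section 7.4 says that "multiple imputation procedures for the laboratory data will be used". Naming a method for laboratory data does not rule out another for AAD. That method, sensitivity analyses and a per-protocol analysis may sit in an analysis plan that is not shown.
- The 10% dropout covers all causes across the trial. No figure is given for withdrawals under this rule, and 5.5.5 describes inpatients in the previous study as very compliant. The bounds in step 4 would apply to any trial with 10% loss, and the 6.1-point end needs an extreme split.
- Two days, three days and more than three days can be read as a coherent graded scale. What remains unclear is consecutive versus cumulative days, and the mandatory wording of 5.5.5 against the discretionary wording of 14.2.
- Ward staff monitor bowels daily, so part of the data may exist whatever the rule says. That makes the fault a missing retention rule, not an inevitable loss.

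These points limit the size and wording of the concern. They do not remove it: no section provides AAD follow-up to day 30 after removal for missed drinks.

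**Conclusion.** The point holds in a limited form. Followed as written, the withdrawal rule leaves the primary outcome unobserved, for at least 23 days of the window, in patients who are free of AAD when removed for missed drinks. They are selected after randomisation by an event that may be related to outcome. This undermines the intention-to-treat comparison for those patients; it does not show that the whole analysis is something else. Section 14.2 mitigates it only in part.

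The size cannot be fixed from the protocol because the number affected is not given, and it is expected to be low. The range of 6.1 to 26.1 points is an upper illustration that assigns the entire all-cause dropout to unobserved outcomes. The 2.6 to 4.9 point bias rests on assumed risks in withdrawn patients and can run in either direction.

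**What to change.** Separate stopping the drink from leaving the study. State that:

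- missed drinks are recorded as non-compliance and do not by themselves end outcome collection;
- stool monitoring and visits continue to day 30 after antibiotics unless the patient withdraws consent;
- ward stool-chart data are retrieved for patients already withdrawn, where consent allows;
- all patients are analysed as randomised.

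Reconcile 5.5.5 and 14.2 on consecutive versus cumulative missed days, and on whether removal for non-compliance is mandatory or discretionary. None of this changes when the product is stopped.

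**Cost.** A short amendment and some extra follow-up records. Participants are inpatients expected to stay more than 6 weeks, and Appendix 2 already schedules daily bowel monitoring. The current version is dated 08 May 2018 with completion expected in Q3 2018, so prospective follow-up would reach few patients and chart retrieval is the main practical step.

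Keeping non-adherent patients may dilute the effect. If 10% of LcS patients reverted to the 56.3% risk, the LcS rate would be 40.2% and power at 180 per arm about 86.7%. That compares with 92.9% at 180 per arm under the planned rates, and 90.1% with 162 observed.

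### Patients who miss the drink for more than 3 days are withdrawn from the study, and nothing secures their AAD outcome for the promised intention-to-treat comparison

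*Protocol*

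**What the plan says.** Four places bear on the point, all in the Protocol.

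- **Section 5.5.5** grades compliance. Two consecutive missed days are minor non-compliance; major non-compliance is "3 consecutive days not drinking". It then states: "If a patient misses intervention for more than 3 days, they will be withdrawn from the study". The sentence after that reads "We will analyse the data using intention-to-treat principle", and section 7.4 repeats it.
- **Section 6.1** runs the primary outcome, any occurrence of AAD, to 30 days after antibiotics finish.
- **Section 14.2** covers removal: "Non-compliance with the protocol or occurrence of significant adverse events may also necessitate discontinuation from the study". For a patient permanently removed, "a study closing assessment should be performed if possible, and all results must be obtained". Continued follow-up is promised only to patients removed for an adverse event, and only until that event resolves.
- **Section 14.3** covers early termination of the whole trial. There the protocol does order follow-up of every enrolled patient through the last scheduled visit.

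The data collection summary (Appendix 2) has stool type and occurrence of diarrhoea recorded daily. Section 5.5.5 has health care staff monitoring bowel function throughout.

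**The concern.** The rule ends participation in the study, not only the study drink, and the trigger is behaviour after randomisation. Intention-to-treat needs an outcome for everyone randomised. Promising that analysis does not supply the data if sites have been told that the patient has left the study.

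The patients concerned are unlikely to be a random sample. A patient may stop drinking because of feeling unwell, becoming nil by mouth or tiring of a long antibiotic course, and each could plausibly be related to the risk of AAD or to the product. If the first AAD episode falls after withdrawal and is not recorded, the arms are compared on incomplete and possibly selected data. A later analysis plan can decide how to handle such patients, but it cannot recover stool records that were never made. The only imputation named in section 7.4 is for laboratory data.

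**Working it through.** **1. The plan's own figure.** Inputs from section 7.2: 56.3% v 38.4%, alpha 0.05 (taken as two-sided, since sidedness is not stated), power 90%, dropout 10%. With mean rate 0.4735 and pooled variance:

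n = [1.96·√(2·0.4735·0.5265) + 1.2816·√(0.563·0.437 + 0.384·0.616)]² / 0.179² = (1.96·0.7061 + 1.2816·0.6947)² / 0.0320 = 161.4, so 162 per arm. Then 162/0.9 = 180.

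Both figures reproduce. Power is 90.1% at 162 analysed per arm and 92.9% at 180.

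**2. Is the outcome secured after withdrawal?**

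| Situation | What follows |
|---|---|
| AAD before withdrawal | Recorded by daily charting; counts |
| Withdrawn for non-compliance | Closing assessment if possible; all results to be obtained; no mention of continued charting |
| Removed for an adverse event | Followed until the event resolves |
| Trial stopped early | Followed to the last visit |

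The duty to follow to the end is written for the last case and not for the second. The gap is a first AAD between withdrawal and 30 days after antibiotics.

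**3. How many patients?** The documents give no rate. Assume each daily drink is missed independently with probability 5% to 10%. The drink continues for 7 days after antibiotics, so courses of 7, 14 and 42 days (assumed) give 14, 21 and 49 drink days.

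| Drink days | More than 3 missed in total | Run of 4 or more missed |
|---|---|---|
| 14 | 0.4% to 4.4% | 0.007% to 0.10% |
| 21 | 1.9% to 15.2% | 0.01% to 0.16% |
| 49 | 23% to 74% | 0.03% to 0.41% |

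The total column is the binomial tail P(X ≥ 4); the run column comes from a day-by-day recursion. Real misses cluster during illness, so independence understates runs. The contrast shows that the missing word 'consecutive' decides how often the rule applies.

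**4. What could unrecorded outcomes do?** Let a share u of each arm have unknown AAD status and let the rest show the planned rates. Putting all unknowns at AAD in one arm and at no AAD in the other bounds the difference:

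17.9·(1 − u) ± 100·u points.

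- u = 2%: 17.5 ± 2, or 15.5 to 19.5
- u = 5%: 17.0 ± 5, or 12.0 to 22.0
- u = 10% (the plan's dropout figure, used as illustration): 16.1 ± 10, or 6.1 to 26.1

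These are extremes, not expected values. They show that the direction is open.

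**5. Does keeping these patients cost the power?** Suppose all 180 per arm are followed and a share w of the LcS arm has the comparator risk. The LcS rate becomes 0.384·(1 − w) + 0.563·w.

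- w = 2%: 38.8%, power 91.8%
- w = 5%: 39.3%, power 90.1%
- w = 10%: 40.2%, power 86.7%

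With 10% lost at random and no dilution, power is 90.1%. With 10% lost and 5% diluted, it is 86.9%.

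**The case against.** The best defence rests on section 14.2. It requires all results to be obtained, and the closing assessment it names can be read as that of section 5.5.7, which includes follow-up at 30 days after antibiotics and bowel monitoring throughout. On that reading a withdrawn patient may still be owed the day-30 assessment. This stands as a possible reading. It is qualified by 'if possible', however, does not mention daily charting or the AAD window, and sits beside an explicit follow-up promise for adverse-event removals only. Sites could reasonably read it either way.

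The defence also holds that the rule bites rarely. It follows two definitions in consecutive days, so it reads naturally as the next step, and the drink is given by a nurse to inpatients whom the protocol calls very compliant in the earlier study. That is fair and limits the size. Likewise, 'may' in 14.2 can be a general clause beside a specific rule, and how withdrawn patients enter the analysis set can be left to an analysis plan that is not shown.

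A reader might infer more than the text supports:

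- **That AAD is not observed at all in non-adherers.** Episodes before withdrawal are charted daily and count. If diarrhoea itself caused the missed drinks, the event has usually been recorded already.
- **That intention-to-treat and 90% power cannot both hold.** They can: step 5 gives 90.1% with 5% of LcS patients at the comparator risk. The 86.7% needs an assumed 10%. If the pilot's 38.4% came from everyone allocated LcS, ordinary non-adherence is already in it; the documents do not say.
- **That a quarter to three-quarters of long-course patients would be withdrawn.** This needs the non-consecutive reading, an assumed miss rate and an assumed 42-day course.
- **That the bias has a known direction or size.** Any such figure needs differential withdrawal rates that the documents do not give, and usually an adherers-only comparison that the protocol does not plan.

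**Conclusion.** The point stands in limited form and should be fixed. The protocol withdraws patients from the study for non-adherence after randomisation, promises intention-to-treat, and does not clearly secure the primary outcome for those patients after withdrawal. A first AAD in that period may be missed for reasons related to treatment or outcome, and the resulting bias could go either way.

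The size cannot be fixed from the documents. On the consecutive reading the number affected is probably small; on the literal reading it could be material for long courses. The illustrative ranges in step 4 rest on assumed shares of unknown outcomes. The sample size of 162, inflated to 180 per arm, is correct on its own inputs, and this point calls for no change to section 7.2.

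**What to change.** In sections 5.5.5 and 14.2, state that non-compliance does not end study follow-up. Suggested wording: 'A patient who meets the non-compliance criterion is recorded as such. Whatever happens to the study drink, daily stool charting and the assessments at 7 and 30 days after antibiotics continue to the end of the AAD window unless the patient withdraws consent, and the patient is analysed in the arm to which they were randomised.'

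Reconcile the compliance passages: three consecutive days against more than three days with no mention of consecutive, and 'will' in 5.5.5 against 'may' in 14.2. Which threshold applies, and what happens to the drink, is for the investigators to decide; the text needs to say one thing. Section 14.2 should also say when the closing assessment takes place and which results are to be obtained.

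The cost is a short amendment and a note to the three sites. The patients are inpatients whose stools are already charted daily, so no new procedure is needed. The extra work is continued charting and the scheduled assessments for the patients concerned.
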